## Abstract

**Background:**

The Lung Cancer Risk Test (LCRT) trial is a prospective cohort study comparing lung cancer incidence among persons with a positive or negative value for the LCRT, a 15 gene test measured in normal bronchial epithelial cells (NBEC). The purpose of this article is to describe the study design, primary endpoint, and safety; baseline characteristics of enrolled individuals; and establishment of a bio-specimen repository.

**Methods/Design:**

Eligible participants were aged 50–90 years, current or former smokers with 20 pack-years or more cigarette smoking history, free of lung cancer, and willing to undergo bronchoscopic brush biopsy for NBEC sample collection. NBEC, peripheral blood samples, baseline CT, and medical and demographic data were collected from each subject.

**Discussion:**

Over a two-year span (2010–2012), 403 subjects were enrolled at 12 sites. At baseline 384 subjects remained in study and mean age and smoking history were 62.9 years and 50.4 pack-years respectively, with 34 % current smokers. Obstructive lung disease (FEV1/FVC <0.7) was present in 157 (54 %). No severe adverse events were associated with bronchoscopic brushing. An NBEC and matched peripheral blood bio-specimen repository was established.

The demographic composition of the enrolled group is representative of the population for which the LCRT is intended. Specifically, based on baseline population characteristics we expect lung cancer incidence in this cohort to be representative of the population eligible for low-dose Computed Tomography (LDCT) lung cancer screening. Collection of NBEC by bronchial brush biopsy/bronchoscopy was safe and well-tolerated in this population. These findings support the feasibility of testing LCRT clinical utility in this prospective study. If validated, the LCRT has the potential to significantly narrow the population of individuals requiring annual low-dose helical CT screening for early detection of lung cancer and delay the onset of screening for individuals with results indicating low lung cancer risk. For these individuals, the small risk incurred by undergoing once in a lifetime bronchoscopic sample collection for LCRT may be offset by a reduction in their CT-related risks. The LCRT biospecimen repository will enable additional studies of genetic basis for COPD and/or lung cancer risk.

**Trial registration:**

The LCRT Study, NCT 01130285, was registered with Clinicaltrials.gov on May 24, 2010.

**Electronic supplementary material:**

The online version of this article (doi:10.1186/s12890-016-0178-4) contains supplementary material, which is available to authorized users.

## Background

Lung cancer claimed nearly 160,000 lives in 2014 in the United States alone [1]. Prevention efforts have reduced cigarette smoking prevalence from about 50 % in 1960 to less than 20 % today but, due to past and continued cigarette smoking and the lack of effective treatment for advanced disease, lung cancer kills more than the next three most deadly cancers (breast, colon, prostate) combined and is expected to do so for decades to come [1]. Because prognosis is related to stage, there has long been interest in detecting lung cancer in early stage when it is amenable to potentially curative treatment. Thus, it is notable that the US Preventive Services Task Force (USPSTF) now recommends lung cancer screening with LDCT for healthy individuals at high risk for lung cancer on the basis of evidence that it will detect the majority of lung cancers in early stage and thereby reduce lung cancer mortality by > 20 % [2, 3]. However, the overall benefit of screening is associated with adverse consequences, including identification of large numbers of nodules, most of which will be nonmalignant, and the complications, costs, and anxiety associated with diagnostic tests [4]. These adverse consequences could be reduced by restricting screening eligibility to only those at greatest risk. Among the approximately 8 million subjects eligible for screening according to current criteria, which include smoking history ≥30 pack-years and age 55–80 years [3, 5], risk varies widely from less than 0.08 % per year to over 1 % per year [6–13]. As such, a large majority of screened individuals will not develop lung cancer in their lifetime and the overall benefit of screening is reduced by the adverse events and large cost associated with screening subjects who will not benefit due to low risk. For these reasons, there is increasing interest in the development of an accurate diagnostic molecular test for lung cancer risk that will more accurately stratify subjects for screening. It is expected that limiting screening to those with a positive risk test will reduce the high cost and side effects of screening programs.

Different approaches are currently in progress to develop a molecular diagnostic test for lung cancer risk in the group eligible for annual CT screening based on demographic criteria. These approaches may be divided into two broad categories, early diagnosis and hereditary risk.

The clinical setting for LCRT biomarker intended use is individuals who are approaching annual CT screening eligibility according to USPSTF criteria [2]. In order to have clinical utility it is important that the test be both accurate and safe to perform in this intended population. In an effort to assess the accuracy and safety of the LCRT we initiated a multi-site prospective cohort trial. The purpose of this report is to describe 1) the LCRT trial study design and primary endpoint, 2) baseline characteristics of enrolled individuals including demographic and lung function data, and 3) secondary endpoints reached thus far, including a) analysis of safety for the bronchoscopic brush method used to obtain samples for LCRT testing, and b) establishment of a biospecimen repository containing NBEC and peripheral blood samples collected from the LCRT cohort.

## Methods

### Study design

This LCRT study (Clinicaltrials.gov, NCT 01130285) was conducted after approval by an institutional review board at each participating institution (University of Toledo Medical Center, Mayo Clinic, University of Michigan, The Toledo Hospital, Ohio State University, Vanderbilt University Medical Center/Tennessee Valley VA Medical Center, Henry Ford Health System, National Jewish Health, Medical University of South Carolina, Inova Fairfax Hospital, Cleveland Clinic Foundation and Mercy St. Vincent Medical Center, see Additional file 1: Table S1) and under a Federal Drug Administration (FDA) approved Investigational Device Exemption (IDE G090273). The original design to assess the clinical utility of the LCRT biomarker was a prospective, blinded, nested case–control study. The original primary endpoint was prediction of risk for development of lung cancer with an odds ratio of at least 5.0. It was estimated that there would have been sufficient power to test this endpoint by enrolling approximately 800 subjects and following them for 3 years, resulting in identification of at least 15 prospective lung cancer cases. LCRT analysis would then be conducted in NBEC of the 15 cases and 120 matched controls. However, the study was revised to a prospective cohort design due to a) advances in technology that enable cost-effective measurement of LCRT in all subjects, and b) the greater power associated with this design. The new design and primary endpoints are described below.

The secondary endpoints and analyses are unchanged and include: 1) determination of study safety at day 30, 2) establishment and maintenance of a biospecimen repository of biological specimens derived from NBEC [RNA and cytology slides] and corresponding blood samples [peripheral blood leukocyte Buffy Coat and frozen plasma] from the subjects enrolled, 3) analysis of the predictive ability of LCRT positive for lung cancer including sensitivity, specificity, positive predictive value, and negative predictive value, 4) calculation of absolute risk of LCRT positive for lung cancer and, 5) measurement of the incidence of lung cancer in the study cohort every two years until the end of study. Additionally, we will explore the influence of demographic or clinical variables for lung cancer on the predictive ability of LCRT.

### Revised study design

After development of a novel targeted NGS platform [29], we implemented LCRT measurement on this platform. The higher throughput of the NGS method enables cost-effective analysis of samples from all 384 subjects and conversion to a prospective cohort study with greater power compared to the original nested case–control design. We plan to assess association of the LCRT value with development of lung cancer in this cohort through follow-up every one to two years for up to 20 years. We will estimate disease-free probabilities for different measured LCRT values at six and eight years of follow up. The primary endpoint will be the prediction of risk for development of lung cancer with a risk ratio of at least 5.0 and we expect to reach this endpoint at the six year follow-up.

Assuming a 20 % rate of failure to re-contact (due to death or other factors), approximately 300 individuals from the cohort will be available for analysis. Based on the demographic characteristics of the LCRT cohort, the expected cumulative incidence at six years following enrollment (which will be reached for all subjects between 2016 and 2018) is >5 %. Assuming a two-tailed test of significance and a type-1 error rate of 0.05, there will be >80 % power to detect a risk ratio associated with LCRT positivity of ≥ 2.45, 1.82, 1.65, 1.57, 1.49, and 1.42 for cumulative incidence rates of lung cancer of 1 %, 2 %, 3 %, 4 %, 5 %, and 6 %, respectively, in the cohort at the six year follow-up. Thus, this proposed study is more than adequately powered to detect even modest LCRT effects at the next planned follow-up. In addition to the risk ratio associated with a positive LCRT, we will also calculate the concordance index of the test based on the estimated Cox proportional hazards model. The concordance index in the Cox model is the correlate to the area under the receiver operator characteristic curve for a logistic regression model. We will use it to measure LCRT biomarker accuracy in the full cohort analysis.

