### Follow up

Subjects enrolled into the study were followed at 30 days for adverse events (AE) and serious adverse events (SAE) possibly related to the study procedure and then every 3 months throughout the first two years following enrollment. A research driven CT was done at the one and two year anniversaries of enrollment if a standard of care CT was not done within three months of the anniversary. The next follow-up is planned for 2016 with another in 2018. At each follow-up subjects will receive medical record review and phone interview. Those who meet USPSTF guidelines will be encouraged to enter the closest CT screening program for early detection of lung cancer. Those who do not meet current reimbursement criteria for CT screening will receive a study driven chest CT.

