### Establishment of NBEC and peripheral blood sample biospecimen repository

Matched blood and NBEC were collected for 361/384 (94 %) subjects and banked in multiple aliquots. Blood samples were processed at each site at the time of collection to generate 2 aliquots of buffy coat and 2–5 aliquots of plasma from each subject. These aliquots were frozen and stored at −80 °C until shipment to the Early Detection Research Network (EDRN) Biorepository in Fredrick, MD. One aliquot of buffy coat was transferred to the University of Toledo for analysis and the other remains in storage. NBEC were stabilized at each site in RNA Later (Ambion, Austin, TX) and shipped along with matching slides to ResearchDx, Irvine, CA. RNA was extracted from NBEC within 24–48 hours of receipt, assessed for quality and quantity and stored in aliquots at −80 °C. One NBEC RNA aliquot was shipped to the University of Toledo for analysis for those samples with a minimum yield of 1 microgram and aliquots for each subject remain in storage at ResearchDx.

At the University of Toledo, genomic DNA (gDNA) was extracted from one aliquot of buffy coat derived from the blood sample from approximately 80 % of subjects and 100 % of these yielded gDNA of sufficient quality and quantity for proposed molecular studies. The quality and quantity of NBEC RNA from approximately 40 % of subjects has been assessed to date. RNA from each sample was treated with DNase I, tested via PCR to ensure removal of contaminating gDNA from the RNA and then reverse transcribed into cDNA. For 90 % of subjects the cDNA generated from these purified NBEC RNA samples was PCR amplifiable and of sufficient quantity to perform LCRT testing. Additional aliquots of RNA remain for the roughly 10 % of samples that did not pass this quality control. Samples from over 120 subjects were used successfully in preliminary targeted next generation sequencing (NGS) RNA sequencing analysis studies.

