### Feasibility to reach LCRT study endpoint based on cohort characteristics

Based on demographic characteristics of the enrolled population (Table 1), we expect lung cancer incidence in the LCRT study to be similar to the 3.1 % incidence over 3.9 years reported by Bach et al. [40] in which mean age was 60.1 and smoking history of 52 pack-years. The five incidental lung cancers observed two years after initiation of the study are consistent with this rate. Taking into account that some of the 384 study subjects will have died from causes other than bronchogenic carcinoma prior to these time points and that some will be lost to follow up we estimated incidental lung cancers in the cohort based on 300 subjects. As such we expect to observe approximately 12 incidental lung cancers by the 2016 follow up (mean time since enrollment approximately 5 years) and 17 by the 2018 follow up point (mean time since enrollment approximately 7 years), which will be more than sufficient to reach the proposed endpoint of a risk ratio of ≥ 5.0.

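### The six-year power statement is applied to the 2016 visit, which by the plan's own figures is at a mean of about five years with about 12 cancers, not more than 15

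*Protocol article*

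**What the plan says.** The Revised study design section sets the primary endpoint as a risk ratio of at least 5.0, to be reached at the six-year follow-up. Its planning inputs are:

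- Sample size: "Assuming a 20 % rate of failure to re-contact (due to death or other factors), approximately 300 individuals from the cohort will be available for analysis".
- Incidence: "the expected cumulative incidence at six years following enrollment (which will be reached for all subjects between 2016 and 2018) is >5" per cent.
- Test: two-sided, type-1 error 0.05.

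The section concludes that the study is more than adequately powered at the follow-up that comes next. It gives "cost-effective analysis of samples from all 384 subjects" as a reason for the change to a cohort design.

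Other sections bear on these inputs:

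- Follow up: "The next follow-up is planned for 2016 with another in 2018".
- Feasibility to reach LCRT study endpoint: "we expect lung cancer incidence in the LCRT study to be similar to the 3.1 % incidence over 3.9 years" of a published smoker cohort. From this it projects, in 300 subjects, about 12 cancers by 2016 (mean about 5 years) and 17 by 2018 (mean about 7 years).
- Results, Enrollment: accrual was completed in March 2012.
- Biospecimen repository: "Matched blood and NBEC were collected for 361/384 (94 %) subjects". For 90% of the subjects assessed so far (about 40% of the cohort), the "cDNA generated from these purified NBEC RNA samples was PCR amplifiable and of sufficient quantity to perform LCRT testing".

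**The concern.** The Methods section and the Feasibility section describe different amounts of information for the same analysis. Methods takes a six-year incidence above 5% and applies the resulting power to the next visit. Feasibility gives that visit a mean of about five years and 12 cancers. A reader cannot tell which visit carries the primary analysis, and no planned visit falls at a mean of six years.

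The number of cancers determines power. If the 2016 data are analysed as the six-year result, the test of the primary endpoint rests on fewer events than the power paragraph implies. The denominator also leaves no room for subjects who are re-contacted but have no usable LCRT value.

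**Working it through.** **1. Figures that reproduce.**
- Analysable N: 384 × 0.80 = 307, so about 300 is fair for loss to re-contact alone.
- Reference rate: 3.1% / 3.9 years = 0.795% per year.
- 2016: 300 × 0.795% × 5 = 11.9. 2018: 300 × 0.795% × 7 = 16.7. These are the stated 12 and 17.

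**2. Six-year incidence.**
- Linear: 0.795% × 6 = 4.77%.
- Constant hazard: 1 − (1 − 0.031)^(6/3.9) = 4.73%.
- From the plan's own counts: 12/300 × 6/5 = 4.80%; 17/300 × 6/7 = 4.86%.
- Time to reach 5%: 5 / 0.795 = 6.3 years.

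So the rate that reproduces 12 and 17 does not give more than 5% at six years. In 300 subjects it gives 300 × 4.77% = 14.3 cancers, against more than 15.

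**3. Timing.** The next visit is 2016, where 12/300 = 4.0%. Only subjects enrolled in 2010 can have completed six years by the end of 2016. The last ones enrolled, in March 2012, complete six years in March 2018.

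**4. Power for a risk ratio of 5.** Schoenfeld approximation, two-sided 0.05: power = Φ(√(d·p·(1−p)) × ln 5 − 1.96), with d events and p the LCRT-positive share. The article gives no p, so 50% and 25% are assumed.

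| Events d | Basis | p = 50% | p = 25% |
|---|---|---|---|
| 15 | 5% of 300 | 88% | 77% |
| 14.4 | 4.8% of 300 | 86% | 75% |
| 12 | 2016, N = 300 | 80% | 67% |
| 10.4 | 4.0% of 260 | 74% | 61% |
| 17 | 2018, N = 300 | 91% | 82% |

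The first row for p = 50% is √(15 × 0.25) × 1.609 − 1.96 = 1.16, and Φ(1.16) = 0.88. The last row is √(17 × 0.25) × 1.609 − 1.96 = 1.36 for p = 50% and √(17 × 0.1875) × 1.609 − 1.96 = 0.91 for p = 25%.

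**5. Analysable N once the assay is considered.**
- No assay loss: 384 × 0.80 = 307.
- All 23 subjects without a matched pair (384 − 361) lack NBEC, and every QC failure is rescued: 361 × 0.80 = 289.
- All 384 have NBEC, and no QC failure is rescued: 384 × 0.80 × 0.90 = 276.
- Both losses: 361 × 0.80 × 0.90 = 260.

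At N = 260 the expected cancers are 260 × 3.97% = 10.3 in 2016 and 260 × 5.56% = 14.5 in 2018.

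**The case against.** **The gap in incidence is small.** The difference between 5% and 4.8% is under one cancer in 300 and costs 1 to 2 points of power. It rests on a constant rate, which the article does not state. The cohort is also older than the reference cohort (mean 62.9 against 60.1 years), which could justify a higher figure. This stands as to size. But the article itself calls the two incidences similar, and its 12 and 17 follow from the unadjusted rate.

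**The dates are stated correctly.** The quoted parenthesis, that all subjects reach six years between 2016 and 2018, is right, and the Feasibility section openly gives mean times of about 5 and 7 years. This stands too. The conflict is confined to applying the six-year power claim to the next visit.

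**Lower incidences are covered.** The power paragraph lists detectable ratios for incidences from 1% to 6%, so 4% is among them. Whether those ratios can be reproduced is a separate matter and is not relied on here. Listing 4% does not say which visit carries the primary analysis.

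**Choice of analysis visit belongs in a SAP.** Often so. Here, however, the article itself fixes six years and attaches the claim to the next visit, so the contradiction is in the text shown.

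Three stronger readings are tempting and are not supported:

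- *That the analysable number is really 260 to 276.* That is the worst case. Spare RNA remains for the samples that failed QC, and only about 40% of subjects had been assessed. The 361 counts matched blood and NBEC pairs, whereas LCRT needs only NBEC. Enrolment was defined by NBEC collection, so the missing sample may be blood. The phrase about all 384 subjects concerns throughput and cost and does not claim that every sample is usable.
- *That 2016 would have only about two thirds of the implied cancers.* This needs the worst-case N. At N = 300 the ratio is 12/15, or four fifths.
- *That the 5 cancers already seen project to 3.9% at six years (5/384 × 3).* This assumes two full years of follow-up for everyone. The cases are dated two years from the start of the study, while accrual ran from 2010 to 2012. With a mean of one year, the same count projects to about 7.6%. It settles nothing.

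**Conclusion.** The point holds in a limited form. The power statement for the primary endpoint does not match the article's own inputs. The visit it refers to has about 12 expected cancers at a mean of about five years, not more than 15 at six years. For a risk ratio of 5 this costs about 8 to 10 points of power before any assay loss. The overstatement of six-year incidence is real but minor. The figure of 300 is arithmetically sound for re-contact loss and lies near the upper end of a range of about 260 to 307, because nothing is allowed for assay failure.

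These conclusions assume a constant incidence rate, the Schoenfeld approximation and an LCRT-positive share of 25% or 50%. The mismatch over timing depends on none of these, since it follows directly from the article's own dates and event counts.

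**What to change.** 1. Restate the expected six-year incidence as about 4.8%, naming the reference rate and the constant-rate assumption.
2. Give expected cancers as about 12 (2016) and 17 (2018) at N = 300, falling to about 10 and 14 to 15 at the worst-case N of 260.
3. Give analysable N as a range of about 260 to 307 with an explicit allowance for assay failure. State whether the 23 unmatched subjects lack NBEC or blood.
4. Replace the reference to the next follow-up. Place the six-year primary analysis at the 2018 visit, once the last subjects enrolled have completed six years (March 2018), and describe the 2016 results as descriptive.

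No new data collection is needed, because the 2018 visit is already planned. The stated figures become slightly less favourable, and the formal analysis falls at the later visit.

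### The claimed >80% power for LCRT-positivity risk ratios of 1.42 to 2.45 does not hold: about 300 subjects at 1–6% incidence yield only 3 to 18 cancers, and power for a positive/negative contrast is then under about 20%

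*Protocol article*

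**What the plan says.** All of the power statement is in the protocol article, Methods, Revised study design; the Statistical analysis section only refers back to it.

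- Sample: "approximately 300 individuals from the cohort will be available for analysis", after a 20% allowance for failure to re-contact the 384 subjects.
- Test: "Assuming a two-tailed test of significance and a type-1 error rate of 0.05".
- Claim: "there will be >80 % power to detect a risk ratio associated with LCRT positivity of ≥ 2.45, 1.82, 1.65, 1.57, 1.49, and 1.42", paired in order with values "for cumulative incidence rates of lung cancer of 1 %, 2 %, 3 %, 4 %, 5 %, and 6 %, respectively, in the cohort" at six years.
- Conclusion: "this proposed study is more than adequately powered to detect even modest LCRT effects at the next planned follow-up".

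The Abstract describes the comparison as one between people with a positive and people with a negative test value. The primary endpoint is a risk ratio of at least 5.0, and incidence at six years is expected to exceed 5%. The Discussion (Feasibility to reach LCRT study endpoint based on cohort characteristics) forecasts cases on the same base of 300: "we expect to observe approximately 12 incidental lung cancers by the 2016 follow up", and 17 by 2018. The share of subjects expected to be LCRT-positive is not given.

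**The concern.** Power for a time-to-event comparison depends on the number of events, and here that number is very small. Ratios near 1.5 normally need well over a hundred events, whereas the listed incidences supply at most 18. The 1% row can be checked without any power formula. With 3 cancers and a 150/150 split, even if all three fall in the positive group, the two-sided Fisher p-value is 0.25. No ratio, 2.45 included, can then reach significance.

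What is at stake is how the next follow-up will be read. With 12 cancers and an estimated ratio of 1.0, the upper 95% limit would be about exp(1.96/√(12 × 0.25)) = 3.1 with half the subjects positive, or exp(1.96/√(12 × 0.1875)) = 3.7 with a quarter positive. A reader who trusts the printed list could take such a result as excluding ratios near 1.5. The test is proposed as a basis for delaying screening in people at low predicted risk, so that misreading would matter.

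**Working it through.** **Inputs.** From Revised study design: N = 300, two-sided α = 0.05, target power 80%, six incidence/ratio pairs, Cox model. Assumption: the share positive, p, lies between 10% and 50%. Under Schoenfeld, p = 50% is the most favourable value.

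**Step 1: events.** d = 300 × incidence = 3, 6, 9, 12, 15, 18. The Discussion's forecast of 12 and 17 cases is on the same scale.

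**Step 2: try to reproduce the stated power for a binary test.** Power = Φ(√(d·p(1−p))·ln RR − 1.96). First row, p = 0.5: √(3 × 0.25) = 0.866; × ln 2.45 (0.896) = 0.776; − 1.96 = −1.184; Φ = 11.8%.

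**Step 3: events needed at p = 0.5.** d = (1.96 + 0.842)² / (0.25 × (ln RR)²) = 31.4/(ln RR)². For RR 2.45: 31.4/0.803 = 39.1.

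**Step 4: what predictor SD would give exactly 80%?** SD = 2.80/(ln RR × √d). For RR 2.45: 2.80/(0.896 × 1.732) = 1.81.

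| Incidence | Cancers | Stated RR | Power, p = 50% | Events needed for 80%, p = 50% | Implied SD |
|---|---|---|---|---|---|
| 1% | 3 | 2.45 | 11.8% | 40 | 1.81 |
| 2% | 6 | 1.82 | 11.0% | 88 | 1.91 |
| 3% | 9 | 1.65 | 11.3% | 126 | 1.86 |
| 4% | 12 | 1.57 | 11.9% | 155 | 1.79 |
| 5% | 15 | 1.49 | 11.7% | 198 | 1.81 |
| 6% | 18 | 1.42 | 11.2% | 256 | 1.88 |

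With 20% positive, power is 8.5–9.1%; with 10% positive, 6.4–6.8%. The events needed exceed those available by a factor of about 13 to 15.

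**Step 5: other readings.**
- Fisher exact, 300 subjects: at most 18%.
- Two-proportion normal approximation, 300 subjects: about 10–18% if the incidence is the overall rate, up to about 20% if it is the rate in LCRT-negatives.
- One-sided α: at most 19% (Schoenfeld).
- All 384 subjects, no loss: at most 14% (Schoenfeld), about 23% (most generous two-proportion reading).
- Incidences read as annual rates over six years: 44–48%.

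No reading as a binary test reaches 80%.

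**Step 6: the likely origin.** A binary predictor has SD √(p(1−p)), at most 0.5. The implied SDs cluster at 1.79–1.91, and a continuous covariate with SD 1.85 gives power of 77–82% in all six rows. On that reading the ratios are per unit of score. Per one SD they would be 1.42^1.85 = 1.9 up to 2.45^1.85 = 5.2, so not all are modest. If the listed ratios were instead per SD, power would be 31–35%.

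**Step 7: the primary ratio of 5.0.** Schoenfeld power:

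| Share positive | 12 cancers | 17 cancers |
|---|---|---|
| 50% | 80% | 91% |
| 20% | 61% | 76% |
| 10% | 39% | 51% |

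The formula is a large-sample approximation and is unreliable at these counts. Exact check for 12 cancers, 50% positive: Fisher rejects in the harmful direction when at least 10 of 12 fall in positives. At RR 5 each cancer falls there with probability 5/6, so power = P(Bin(12, 5/6) ≥ 10) = 0.296 + 0.269 + 0.112 = 68%, not 80%.

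**The case against.** **The figures may be a sound calculation under a wrong label.** The section also speaks of measured LCRT values and plans a Cox model, and one continuous-covariate calculation fits all six ratios. An article condenses, so the score's SD could sit in the full protocol. This is plausible and is why the arithmetic itself should not be called impossible. But the printed ratios are tied to positivity, and a per-unit ratio is not a positive-versus-negative ratio. The statement is wrong as written on either explanation.

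**The positive share is unknown, so no single true power can be quoted.** Correct: 6–12% holds for Schoenfeld with 10–50% positive, and other methods run somewhat higher. None comes near 80%.

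**A reader might infer that the revised design is weaker than the original.** The article claims "conversion to a prospective cohort study with greater power compared to the original nested case–control design", while of the original it says "LCRT analysis would then be conducted in NBEC of the 15 cases and 120 matched controls". With only the 12 cases forecast for 2016, an unmatched (Woolf) comparison at an odds ratio of 5 does put the cohort slightly lower: 72%, 75% and 54% against 74%, 80% and 61%, for 10%, 25% and 50% positive. But the power statement is tied to six years and incidence above 5%, hence at least 15 cases in 300. There the cohort gives 80%, 83% and 63%, ahead each time, and with 17 cases 84%, 87% and 68%. The original 15 cases also presupposed about 800 enrolled, against 403 achieved. The documents do not support that inference.

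**A reader might infer that the primary endpoint is lost.** That does not follow either. Power at a ratio of 5.0 may be adequate or poor, depending on the unstated positive share.

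**Conclusion.** The point stands for the six listed ratios and for the conclusion drawn from them. For the positive/negative contrast described, 3 to 18 cancers in about 300 subjects give power of roughly 6–12% by Schoenfeld (10–50% positive assumed) and under about 20% by exact or two-proportion methods, against a claim of more than 80%. At a 50/50 split about 40 to 255 events would be needed. The event counts follow directly from the article; the positive share is an assumption, varied over its plausible range without changing the conclusion. That the ratios are per-unit values for a continuous score is an inference from the implied SD of about 1.8–1.9.

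**What to change.** 1. Replace the list with detectable risk ratios for positive versus negative, computed by a small-sample method (exact or simulation), with the assumed positive share stated. For illustration, Fisher's exact test conditional on the event count gives 80% power at ratios of about 5.7–6.6 with 12 cancers and 4.0–4.7 with 18, for 25–50% positive. The large-sample values at 50% positive (5.0 and 3.75) are too optimistic and should not be printed.
2. Alternatively, if the ratios are per unit of a continuous score, relabel them and state the unit and SD.
3. Delete the sentence concluding that modest effects can be detected at the next follow-up.
4. State power for the primary ratio of 5.0 at the expected 12 to 17 cancers, over a stated range of positive shares.

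The cost is a recalculation and a change of wording. No new subjects or data are needed, but the stated figures become less favourable.
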